### Criteria for discontinuation

2.10

If unexpected adverse events occur, participants should no longer follow the study guidelines for such events. The investigator should comprehensively analyze whether these events are related to the experimental and control drugs used, and should decide whether to discontinue the clinical trial based on the participant’s condition. Patients who discontinue trials owing to serious adverse events should be followed up, and their outcomes should be documented. In addition, participants who could not adhere to the treatment and those who requested active withdrawal, had poor compliance, were pregnant, dead, or lost to follow-up met the criteria for discontinuation.

### Sample size

2.11

This was a randomized controlled trial. The primary outcome was the 2-year disease-free survival (DFS) rate of patients with GC after surgery. It was estimated that the DFS rate 2 years after surgery in the control group was 43.9%, whereas the DFS rate in the intervention group was 63.9%. For α = 0.05 (bilateral), β = 0.2. Assuming that the enrollment rate of the study patients remained unchanged, the proportion of the intervention group to the control group was 1:1. The sample size for N1 was 96 cases in the intervention group, and for N2 was 96 cases in the control group, as calculated using the PASS 11 software. However, a detachment rate of 10% must be considered in the research process. Therefore, the intervention and control groups comprised 106 patients each (212 patients total).

### Outcome measurements

2.12

The 2-year DFS rate as the primary outcome and DFS, OS, 1- to 3-year cumulative recurrence and metastasis rate, and 1- to 3-year cumulative survival rate as the secondary outcome will be calculated at the end of follow-up. The lymphocyte count-to-monocyte count ratio (LMR) (59), lymphocyte count-to-neutrophil count ratio (LNR) (60), prognostic nutritional index (PNI) (61), Quality of Life Questionnaire of Stomach 22 (QLQ-STO22) (62), M. D. Anderson Symptom Assessment Scale Gastrointestinal Tumor Specific Module (MDASI-GI) (63), Postgastrectomy Syndrome Assessment Scale-45 (PGSAS-45) (64) (diagnosis of the syndrome should refer to the 2014 *Guidelines of Diagnosis and Therapy in Oncology with Traditional Chinese Medicine*), and other secondary outcome indicators will be collected at weeks 0–6, whereas the total fat area (TFA) (65), visceral fat area (VFA) (66), subcutaneous fat area (SFA) (67), visceral adiposity index (VAI) (68), and tumor markers will be collected at weeks 0, 3, and 6. All measurement results will be recorded in the case report form (CRF). The details of outcome measurement projects are shown in **Table 1**.

**Table 1 T1:** Treatment stage flowchart.

Item		Baseline	Treatment observation				Follow-up
Number of visits		1st time	2nd time	3rd time	4th time	*N*th time	*N* + *X*th time
Observation time		Days −7 to 0	Days 28–35	Days 56–63	Days 84–91	End of *N*th treatment course	Once every 3 months
Inclusion/Exclusion criteria		√					
Sign informed consent form		√					
Collect medical history							
Demographic data		√					
Diagnosis and TNM classification		√					
Past history and comorbidities		√					
Clinical observation							
Vital signs		√	√	√	√	√	√
Physical examination		√	√	√	√	√	√
Survival situation		√	√	√	√	√	√
MDASI-GI		√	√	√	√	√	√
Tongue and pulse condition		√	√	√	√	√	√
TCM syndrome		√	√	√	√	√	√
Imaging examination	PET-CT/CT/X-ray	√			√	√	√
	MRI, B-mode ultrasonography	*	*	*	*	*	*
	Bone scanning	*	*	*	*	*	*
	Gastroscope	*	*	*	*	*	*
Tumor marker		√	*	*	√	*	*
Indicators related to fat distribution		√	*	*	√	*	*
QLQ-STO22		√	√	√	√	√	√
PGSAS-45		√	√	√	√	√	√
Safety observation							
Blood routine		√	√	√	√	√	√
Hepatic and renal function		√	√	√	√	√	√
Urine and stool routine		*	*	*	*	*	*
Electrocardiogram		√	√	√	√	√	√
NCI adverse reaction			√	√	√	√	√
Adverse event			√	√	√	√	√
Other work							
Efficacy evaluation			√	√	√	√	√
Drug combination			√	√	√	√	√

*This check is optional.

√ This check is necessary.

#### Primary outcome

2.12.1

The primary outcome of this study is the 2-year DFS rate after surgery, which refers to the proportion of patients who have not experienced recurrence, metastasis, or (for any reason) death within 2 years after surgery.

#### Secondary outcome

2.12.2

1. Prognosis related indicators

DFS: Time from randomization to the onset of tumor progression or (for any reason) death in patients.

OS: Time from randomization to death from any cause.

Annual cumulative recurrence and metastasis rate for 1–3 years: The proportion of patients who experience recurrence and metastasis within 1–3 years from the day of surgery to the total number of patients.

Annual cumulative survival rate for 1–3 years: The proportion of patients with a survival period of 1–3 years or more from the day of surgery to the total number of patients.

2. Fat distribution-related indicators

TFA of the abdomen: A CT plain scan will be used to measure the fat area on cross-sectional images, directly reflecting the accumulation of abdominal fat in the human body. It is generally believed that the umbilical plane or L2/L3 gap can better reflect the body’s abdominal fat.

VFA: A commonly used indicator in clinical practice to evaluate the level of visceral fat. The precise measurement method is usually based on imaging methods, specifically the area occupied by adipose tissue in a certain section of abdominal CT (flat umbilical section or third lumbar section).

SFA: SFA = TFA − VFA.

VAI: This is another indicator for evaluating visceral adipose tissue accumulation and dysfunction, and is a new visceral fat assessment index calculated based on waist circumference (WC), body mass index (BMI), triglycerides (TG), and high-density lipoprotein (HDL).

Male VAI = [WC/(39.68 + 1.88 × BMI)] × (TG/1.03) × (1.31/HDL);

Female VAI = [WC/(36.58 + 1.89 × BMI)] × (TG/0.81) × (1.52/HDL).

3. Tumor markers: Carcinoembryonic antigen (CEA), carbohydrate antigen 724 (CA724), and carbohydrate antigen 199 (CA199) should be included as tumor markers.

4. Peripheral blood inflammatory indicators:

LMR: Ratio of lymphocyte count to monocyte count

LNR: Ratio of lymphocyte count to neutrophil count

5. Prognostic nutritional index (PNI): Record serum albumin (ALB) and lymphocyte (TLC) counts, with the formula PNI = ALB + 5 × TLC.

6. Symptoms and quality of life evaluation:

The QLQ-STO22 developed by the European Organization for Research and Treatment of Cancer will be used to evaluate the impact of treatment protocols on the quality of life of GC patients.

The impact of treatment regimens on patient symptoms will be evaluated using the MDASI-GI.

The quality of life with GC patients after gastrectomy will be measured using the PGSAS-45, and the intensity of various symptoms of post-gastrectomy syndrome will be understood.

7. Medication compliance: The number and percentage of cases will be calculated based on <80%, 80%–120%, and >120% medication compliance.

Medication compliance = actual dosage/expected dosage × 100% (rounded to two decimal places).

8. Adverse reaction rate: The proportion of adverse reactions caused by drugs in the enrolled population.

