### Statistical analysis and method

2.16

SAS 9.4 statistical software will be used, and full analysis set (FAS) and protocol compliance set (PPS) analyses will be performed on the efficacy indicators. A safety dataset analysis should be conducted for adverse reactions. All statistical tests will be conducted bilaterally, and statistical significance will be set at *p* ≤ 0.05. We will analyze whether there are outliers in the data and conduct a professional analysis of outliers to decide whether to accept or reject them. After this, we will analyze the data for missing values and conduct a professional analysis to determine whether the missing values are listed as missing or data transferred. The proportion of shedding cases should not exceed 10%; otherwise, analysis and explanation should be provided. The measurement data were described as mean, standard deviation, median, minimum, and maximum whereas counting data were described as frequency, percentage, etc. Quantitative data analysis will be performed using *t*-tests, rank-sum tests, etc. Counting data analysis will be performed using chi-square tests, ridit analyses, etc. Survival data analysis will be performed using the Kaplan–Meier method, Wilcoxon rank sum test, or log-rank test. A Cox-proportional risk regression model was used for multivariate survival analysis.

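### The 1–3-year recurrence and survival rates are defined as crude counts over all patients, so losses to follow-up bias both; the primary 2-year DFS rate has no stated denominator and no single named test

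*Protocol article*

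**What the plan says.** **Secondary rates (Protocol article, 2.12.2).** Annual recurrence and metastasis is "The proportion of patients who experience recurrence and metastasis within 1–3 years from the day of surgery to the total number of patients". Annual survival is "The proportion of patients with a survival period of 1–3 years or more from the day of surgery to the total number of patients". Both name the whole patient count as denominator and start the clock at surgery. The same section runs DFS time and OS from randomization.

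**Primary outcome (2.12.1).** The 2-year DFS rate "refers to the proportion of patients who have not experienced recurrence, metastasis, or (for any reason) death" within two years of surgery. It has no stated denominator and no rule for a patient whose status at two years is unknown.

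**Analysis (2.16).** Count data get chi-square tests, ridit analysis and similar. For time-to-event data, "Survival data analysis will be performed using the Kaplan–Meier method, Wilcoxon rank sum test, or log-rank test". None of these is assigned to the primary outcome. Efficacy is analysed in both the full analysis set and the per-protocol set. For missing data in general, a later professional judgement decides "whether the missing values are listed as missing or data transferred".

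**Follow-up and loss.** Section 2.11 allows for 10% loss, and the Discussion lists likely dropout as a limitation. Section 2.14 plans at least three years of observation after surgery, with imaging ending at recurrence or at the start of another therapy.

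**The concern.** Dividing an observed count by all patients gives every patient lost early a definite outcome. A patient last seen alive and disease-free at month 10 is missing from the numerator of the recurrence rate, so counts as not recurred. The same patient is missing from the numerator of the survival rate, so counts as not surviving. Two adjacent definitions therefore treat one patient in opposite ways, and each rate is pulled below its true value. This is a rule the document states, not a detail left for later.

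For the primary outcome the problem is one of choice. A proportion invites a chi-square test, while the name DFS invites survival methods, and the survival tests are joined by 'or'. The estimate depends on how losses are counted and the p-value on which test is run. In a confirmatory blinded trial, neither should be open once data are seen.

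**Working it through.** **Inputs from the document.** "For α = 0.05 (bilateral), β = 0.2"; "the DFS rate 2 years after surgery in the control group was 43.9"% and "the DFS rate in the intervention group was 63.9"%; 1:1 allocation; 96 per arm raised to 106 for 10% loss (2.11).

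**Assumptions not in the document.** Exponential event times; independent exponential loss; 10% meaning the probability of loss by the stated month if no event came first; 3-year survival of 60%; unequal loss of 5% and 15%.

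**1. The plan's own sample size.** Pooled two-proportion formula, mean rate (0.439 + 0.639)/2 = 0.539:

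n = [1.960·√(2·0.539·0.461) + 0.842·√(0.439·0.561 + 0.639·0.361)]² / 0.20² = 96.3 per arm, against 96 stated.

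Log-rank, Freedman: HR = ln 0.639 / ln 0.439 = 0.544. Events = (1.960 + 0.842)²·[(1 + 0.544)/(1 − 0.544)]² ≈ 90. Patients per arm = 90/(0.561 + 0.361) ≈ 98.

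For loss, 96 × 1.1 = 105.6, or 106 as stated; 96/0.9 = 106.7. The size reproduces, but it fits a comparison of proportions and a log-rank test about equally, so it does not show which is intended.

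**2. Annual survival as written.** A survivor is counted only if still under observation: S × (1 − L).
- 10% lost by month 36: 0.60 × 0.90 = 54.0%.
- 10% lost by month 24 with loss continuing at that rate: 0.60 × 0.90^1.5 = 51.2%.

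**3. Primary rate at month 24, 10% loss in each arm.** With λ = −ln(S)/24 and μ = −ln(1 − L)/24:

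P(event observed) = λ/(λ + μ) × [1 − S(1 − L)].

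Control: λ = 0.0343, μ = 0.00439; 0.8865 × (1 − 0.439 × 0.90) = 53.6%. Intervention: λ = 0.0187; 0.8096 × (1 − 0.639 × 0.90) = 34.4%.

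| Rule for losses | Intervention | Control | Difference |
|---|---|---|---|
| Event-free | 65.6% | 46.4% | 19.2 |
| Failure | 57.5% | 39.5% | 18.0 |
| Excluded | 62.6% | 42.4% | 20.2 |
| True value, recovered by Kaplan–Meier | 63.9% | 43.9% | 20.0 |

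The first row also shows the recurrence bias. If every event were a recurrence, a true control 2-year rate of 56.1% would read 53.6% over all patients.

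**4. Unequal loss (15% control, 5% intervention), same formulas.** Losses as event-free: 64.7 − 47.7 = 17.1 points from unrounded values. Losses as failures: 60.7 − 37.3 = 23.4 points.

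**5. Simulation.** 3,000 trials of 106 per arm, entry at month 8 (assumed), follow-up to month 36, 10% loss.
- Design effect: power is 80.2% for chi-square with losses event-free, 82.2% for the Kaplan–Meier 2-year difference, 93.6% for log-rank and 91.4% for the censored-data Wilcoxon test. Chi-square, log-rank and Wilcoxon do not all agree on significance in 15.6% of trials.
- No effect: these three tests reject in 3.9%, 4.5% and 4.5% of trials, but at least one does in 7.4%.
- No effect, loss 5% against 15%: chi-square counting losses as failures rejects in 10.2%, log-rank in 4.8%.

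**The case against.** The strongest reply concerns the primary outcome. A reader might infer that the 2-year DFS rate is also a crude proportion over all patients, and that its censoring is therefore mishandled. The document does not support that. The whole-patient denominator is written only for the two secondary rates. Kaplan–Meier and log-rank are both listed in 2.16, and a proportion of patients event-free at two years is an ordinary description of what Kaplan–Meier estimates. Censoring for the primary is unresolved, not shown to be wrong, and the exact test and censoring rule could properly sit in an analysis plan that is not shown.

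Three further inferences go too far:
- That the listed Wilcoxon test ignores censoring. Beside Kaplan–Meier and log-rank it plausibly means the censored-data version, although 'rank sum' is the name of the uncensored test.
- That raising 96 to 106 means lost patients will be excluded. That step is routine planning and sets no analysis rule.
- That analysing two sets inflates the type I error. Reporting both is usual practice; harm would come only from picking the better result.

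The size of the effect is also limited. With at least three years of observation, only dropout or stopped imaging hides status at two years, and under equal 10% loss the treatment difference moves little. All of this stands. None of it rescues the secondary definitions: an analysis plan would have to override their wording, not fill a gap.

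**Conclusion.** The point holds firmly for the 1–3-year rates. Their written definitions count a lost patient as recurrence-free in one and as a non-survivor in the other, so recurrence and survival are both understated. For an assumed 60% 3-year survival the understatement is about 6 points with 10% lost by month 36, and about 9 if 10% are already lost by month 24.

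For the primary outcome the conclusion is narrower: the estimator and the test are left open. At equal 10% loss an arm's rate can shift by up to about 6 points and the treatment difference by at most about 2. With the illustrative 15% against 5% loss, a true 20-point difference reads 17.1 or 23.4. Type I error reaches about 7% only if the best of three tests is picked afterwards. These figures rest on exponential times and loss unrelated to prognosis; informative loss would need separate sensitivity analyses, because Kaplan–Meier does not correct for it.

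**What to change.** **Secondary rates.** Define annual survival as Kaplan–Meier estimates at 1, 2 and 3 years, and annual recurrence and metastasis as cumulative incidence with death as a competing event. Run both from surgery, censoring at last contact for survival and at last disease assessment for recurrence.

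**Primary outcome.** Name one estimator and its matching test in the full analysis set: the between-arm difference in Kaplan–Meier 2-year DFS from surgery, with 95% CI and the test of that difference. Make log-rank on DFS time the secondary analysis, with its own origin (randomization) stated, and the per-protocol set a sensitivity analysis. State that a patient with unknown status is censored at the last disease assessment, so that the general missing-value judgement in 2.16 does not reach this outcome.

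**Test list.** Replace the rank-sum entry for survival data by log-rank or an explicitly censored-data Wilcoxon test.

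**Cost.** Wording only; the procedures are standard. The freedom to choose a test is given up, and the 2-year comparison has less power than a log-rank test over all follow-up (about 82% against about 93% under the exponential assumption), though it still meets the planned 80%. Log-rank is not a substitute, because over all follow-up it does not test the 2-year rate.

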**Methods:**

The study will be a multicenter, randomized, double-blind, placebo-parallel-controlled clinical trial. A total of 212 patients who completed adjuvant chemotherapy within 8 months of radical gastrectomy will be enrolled. Patients in the intervention group will receive the YWJP, whereas those in the control group will receive a placebo. The main outcome was the disease-free survival (DFS) rate 2 years after surgery. The secondary outcomes included DFS time, overall survival, annual cumulative recurrence and rate of metastasis after 1–3 years, cumulative annual survival after 1–3 years, fat distribution-related indicators, tumor markers, peripheral blood inflammatory indicators, prognostic nutritional index, symptoms and quality of life evaluation, medication compliance, and adverse reaction rate.

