### Randomization and blinding

2.7

This study will apply an Interactive Web Response System for central randomization and implement hidden allocation schemes. Patients will be randomly divided into intervention and control groups in a 1:1 ratio based on central randomization. The R software (V3.3.3) will be used to generate random sequences with three rounds of cyclic random statements. The blinding level will be double-blind, in which neither the researcher nor the participant have any idea of the specific details of the study. Anonymizing will be performed by statisticians who did not participate in the clinical trials and divided into two levels. This trial will establish a dedicated “emergency letter” for clinical trials that can only be urgently unblinded when the patient experiences an emergency. Handling this situation requires a clear understanding of the patient’s medication information.

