### Safety evaluation

2.13

Safety evaluations were performed according to the National Cancer Institute’s Common Terminology Standard for Adverse Events (CTCAE v.5.0), and patient adverse events were monitored every 3 months from baseline to disease progression, death, or 2 years after surgery. The evaluation methods included routine blood tests, urine tests, biochemical tests, and electrocardiography.

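### The only named safety outcome counts drug-attributed reactions over enrolled patients; the main comparison should be all-cause adverse events among dosed patients, over a common period

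*Protocol article*

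**What the plan says.** Section 2.12.2, item 8, gives the safety outcome: "The proportion of adverse reactions caused by drugs in the enrolled population". The abstract's list of secondary outcomes ends with "medication compliance, and adverse reaction rate" and names no all-cause rate.

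Section 2.16 says "A safety dataset analysis should be conducted for adverse reactions". The article does not define that dataset, which it may properly leave to the full protocol or analysis plan.

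Data collection is wider than the outcome. Table 1 has separate required rows for NCI adverse reactions and for adverse events. Section 2.13 uses CTCAE v5.0 and says "patient adverse events were monitored every 3 months from baseline to disease progression, death, or 2 years after surgery".

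On causality, section 2.10 says of unexpected events: "The investigator should comprehensively analyze whether these events are related to the experimental and control drugs used". Section 2.7 states "The blinding level will be double-blind".

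**The concern.** Randomisation against a blinded placebo already provides the causal contrast: any excess of events in one arm, beyond chance, is due to the treatment. A causality filter adds an opinion that the comparison does not need. These patients enter after gastrectomy and at least six cycles of chemotherapy (2.4), and 2.9 anticipates nausea, vomiting, diarrhoea and liver or kidney dysfunction during the intervention. An investigator judging one patient at a time may find it hard to separate such events from the effects of earlier treatment.

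Two smaller problems sit beside this. The denominator is worded one way in 2.12.2 and another in 2.16. And the monitoring period in 2.13 stops at progression, so a crude proportion depends partly on efficacy. Safety is a stated aim alongside efficacy (abstract and Discussion), so the headline comparison should be one whose meaning is clear.

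**Working it through.** **Plan figures.** The article gives no adverse event rate, attribution share, or number expected to go undosed, so there is no safety figure to reproduce. The inputs taken from it are 106 patients per arm and two-sided α = 0.05 (2.11), DFS at 2 years of 43.9% (control) and 63.9% (intervention) (2.11), and six courses of 4 weeks (2.8). The 106 is the plan's own 96 × 1.10 = 105.6, rounded up. The event rates below are assumptions.

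**1. Effect of attribution on sensitivity.** Two-proportion power with pooled variance under the null and p̄ = (p₁ + p₂)/2:

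power = Φ{[|p₂ − p₁|√n − 1.96√(2p̄(1 − p̄))] / √(p₁(1 − p₁) + p₂(1 − p₂))}, n = 106.

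For all-cause rates of 15% and 30%: (1.544 − 1.157)/0.581 = 0.67, so power is 75%.

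| What attribution removes | Rates compared | Power |
|---|---|---|
| Nothing (all causes) | 15% vs 30% | 75% |
| Half of all events, both arms | 7.5% vs 15% | 41% |
| 70% of all events, both arms | 4.5% vs 9% | 26% |
| 10 points of background in each arm, no excess | 5% vs 20% | 92% |
| Half the background, no excess | 7.5% vs 22.5% | 87% |
| Half the background and a quarter of the excess | 7.5% vs 18.75% | 68% |

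In every row the filter is applied alike in both arms, as blinding implies. Power still moves from 26% to 92%, according to whether true excess events or background events are removed. A second starting point behaves in the same way under equal filtering: 30% vs 45% gives 62%, falling to 29% if half of all events are attributed (15% vs 22.5%).

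**2. Denominator.** If a share u of enrolled patients is never dosed and has no reactions, the rate over the enrolled is r(1 − u). With an assumed r = 20%, u = 0, 2, 5 and 10% gives 20.0, 19.6, 19.0 and 18.0%. The two denominators agree if everyone is dosed and differ by 2 points at u = 10%.

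**3. Length of the monitoring window.** Assume a constant hazard, every patient disease-free at entry (2.4), and no other losses. With entry at 6.5 months after surgery (an assumption within the 8-month limit of 2.4), 17.5 months remain to the 2-year point. Then λ = −ln(S)/17.5 and mean window = (1 − S)/λ.

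- Control: λ = 0.8233/17.5 = 0.0470; 0.561/0.0470 = 11.9 months.
- YWJP: λ = 0.4479/17.5 = 0.0256; 0.361/0.0256 = 14.1 months.
- Ratio 14.1/11.9 = 1.18. The remaining time cancels, so this ratio is the same for any entry time.

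Within the treatment period, t = 24 weeks ≈ 5.5 months, and mean window = (1 − e^(−λt))/λ: 4.9 months (control) and 5.1 months (YWJP), a ratio of about 1.06.

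**The case against.** The strongest reply is that this is a condensed article. All-cause events are recorded and graded, and nothing says that they will not be tabulated by arm. Which tables are produced, how the safety set is defined and whether exposure is adjusted for commonly belong in an analysis plan. That stands against any claim that all-cause events are discarded. It does not answer the point that the article itself fixes the outcome's numerator and denominator in 2.12.2.

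A reader might infer more than the text supports in four places:

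- **That attribution biases the comparison or always lowers power.** Causality is judged blind, so differential bias is not shown. A filter that mainly removes background events raises power, as the table shows.
- **That 2.16 also excludes events not attributed to the drug.** Only 2.12.2 adds drug causation. The article uses the term adverse reaction loosely (Table 1 has an NCI adverse reaction row), so the sentence in 2.16 may cover all CTCAE events.
- **That the two denominators give conflicting numbers.** The safety dataset is undefined here and may coincide with the enrolled set.
- **That the 18% longer window describes this outcome.** It covers the whole period to 2 years after surgery, mostly off treatment. Table 1 also requires adverse events at follow-up visits without stating a stop at progression, and 2.10 follows up patients who discontinue for serious adverse events.

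**Conclusion.** The point holds as a weakness in a stated definition. The one named safety outcome depends on causality opinion that a blinded randomised comparison does not need, although the data for a better comparison are already being collected. The consequence is unpredictable sensitivity: about 26% to 92% power after attribution, against 75% for all-cause events at assumed rates of 15% and 30%. The documents give no event or attribution rates, so neither the direction nor the size can be fixed, and biased results cannot be claimed.

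The denominator is a wording inconsistency to be reconciled. The window effect rests on the plan's DFS assumptions and a constant hazard. It would matter for a crude proportion over the full monitoring period, and is small within treatment. The primary outcome and data capture are unaffected.

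**What to change.** In 2.12.2 and 2.16, name as the main safety comparison the number of patients with at least one adverse event of any cause, by arm, divided by the patients who took at least one dose. Show it for any grade, grade 3 or higher, and serious events. Present drug-attributed reactions as a subset on the same denominator, counting patients, since the present wording leaves open whether patients or events are counted.

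Compare events over the treatment period, or report rates per person-month, so that a difference in time to progression does not feed into the safety result.

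The cost is two sentences of wording and a few extra tables from data already collected. The drawback is that reported event rates will look higher in both arms than attributed rates would.
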